### Randomization, Allocation Concealment, and Blinding

After completing the screening, eligible participants will be allocated randomly to one of two groups: TTM-based health education program group (intervention group) or standard health education group (control group) in a ratio of 1:1 using a computer-generated random number list. The random allocation sequence will be sealed in opaque envelopes by a staff member who will be not involved in study intervention, screening assessments, data collection, or data analysis. Participants will be informed that they will learn facts and management strategies about MCI, and that they will be blinded as to whether they receive health education based on TTM or standard health education. The data collectors and the data analyst will be blinded to group allocations.

### Intervention

#### Intervention Group

The intervention group participants will attend one TTM-based health education session/week, 45–60 min/session for 8 weeks. The TTM encourages an assessment of an individual's current stage of behavior change and provides ten strategies to facilitate the construction of health education content according to the specific behavior stage (27). Therefore, before the intervention, the behavior stage of the participants' cognitive dysfunction management will be assessed by the researcher according to some questions (21) which will guide the researcher to match the appropriate health education contents (see Figure 1). After completing each health education session that matches the current behavioral characteristics, the participant's behavior stage of cognitive dysfunction management will be reassessed, and health education content will be adjusted accordingly. With any behavior change, relapses are common (28), and we will still re-assess the behavior stage and provide stage-matched health education content for participants. The content of health education sessions will be derived from evidence-based knowledge and recommendations will be founded on mild cognitive impairment guidelines (3). The details of this program are displayed in Supplementary Table 1.

**Figure 1 F1:**
[figure not shown]
Overview of the study procedure.

#### Control Group

The control group participants will attend one health promotion session/2 weeks, 45 min/session for 8 weeks that will be delivered by the researcher in another community health care center. The health promotion session will also be derived from evidence-based knowledge and recommendations (3). Each health education session covers different subjects, including basic knowledge of MCI, e.g., the prevalence of MCI, risk factors of MCI, symptoms of MCI, consequences and impacts of MCI, development, and diagnosis of MCI; management strategies of MCI, e.g., taking part in regular exercise (twice/week), encouraging participation in reading, puzzle games, and other cognitive activities, learning basic knowledge of a healthy diet and recommending a Mediterranean diet. For any questions asked by the control participants, general advice, without giving information relating to the behavior change stage and corresponding health education, will be given for ethical consideration.

The staff will record attendance for each participant each session over the 8-week intervention period and ask about the presence of any adverse effects, such as pain or discomfort at each session. The interventions will be delivered at the different sites to minimize experimental contamination among the participants. The study procedure is shown in Figure 2.

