Our study seeks to answer two primary questions:

(1) What are the impacts of a TTM-based health education program on older adults with MCI? We hypothesize that this program would positively affect the level of compliance of participation in cognitive dysfunction management, disease knowledge, and other cognition-related health outcomes (general cognitive function, sleep quality, depression symptoms, apathy symptoms) for older adults with MCI compared to the control group.

(2) Is it feasible to use the TTM-based health education program for recruitment and compliance in the community setting? We hypothesize that older adults with MCI would be unlikely to refuse to participate in this program and would have high compliance, and no adverse events would occur during the intervention.

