#### Data Collection

Before randomized allocation, the baseline data (T0) will be collected at a community health care center by the staff blinded to group allocation, including socio-demographic profile, primary outcomes and secondary outcomes; primary outcomes, and secondary outcomes will be measured again at the end of the intervention (T1) and 3 months after intervention (T2). Table 2 shows the assessment and timeline of the study.

**Table 2 T2:** Summary of study assessments and time-lines.

	**Questionnaire items**	**Time point**				
		**Baseline**	**Randomized allocation**	**Intervention**	**Post intervention**	**Follow-up 3 months**
		**T0**			**T1**	**T2**
Enrollment						
Eligibility screening						
Informed consent						
Screening	**General information**					
	Demographic information	✓				

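### Adverse effects are asked about at sessions, 8 in the TTM arm and 4 in the control arm, so ascertainment differs by arm and by attendance

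*Protocol article*

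**What the plan says.** All references are to the protocol article.

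- **Session schedules.** Intervention Group: "The intervention group participants will attend one TTM-based health education session/week, 45–60 min/session for 8 weeks". Control Group: "The control group participants will attend one health promotion session/2 weeks, 45 min/session for 8 weeks".
- **How adverse effects are found.** The last paragraph under Control Group says "The staff will record attendance for each participant each session over the 8-week intervention period" and that staff will "ask about the presence of any adverse effects, such as pain or discomfort at each session". The paragraph stands under the control heading, but its next sentence deals with the delivery of both interventions at different sites, so it reads as covering both arms.
- **What the information is for.** The second of the two primary questions, at the end of Background, concerns the feasibility of the TTM programme. Part of its hypothesis is that "no adverse events would occur during the intervention".
- **Other contacts.** Under Data Collection, the outcomes are "measured again at the end of the intervention (T1) and 3 months after intervention (T2"). Table 2 lists the instruments by time point and has no adverse-event item at T1 or T2.
- **Other mentions of events.** Study Design and Participants provides for withdrawal after untoward events during the trial or follow-up. Table 1 lists serious events during the intervention period, with stroke and fall as examples. Neither states how such events are to be found.

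**The concern.** The only enquiry described is attached to a visit whose frequency is set by the allocated arm and which takes place only if the participant comes. Two things follow.

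First, the arms are questioned at different intensity. A table of adverse events by arm would mix any true difference with the difference in asking. On this count alone the distortion runs against the TTM programme.

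Second, someone who stops attending is not asked at the sessions missed. Pain, illness or a fall may be the reason for stopping, and the withdrawal provision takes people with events out of the sessions. A finding of no adverse events would then describe those who kept coming and would lean towards confirming the hypothesis. This distortion favours the programme, so the two do not cancel in any predictable way.

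**Working it through.** The article gives no figure for the number of enquiries, so there is none to reproduce. The inputs below come from it, except where marked as assumed.

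**1. Number of asks**

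- TTM arm: 8 weeks ÷ 1 week = 8 sessions, so 8 asks.
- Control arm: 8 weeks ÷ 2 weeks = 4 sessions, so 4 asks.
- With 66 per arm (Sample Size) and full attendance: 66 × 8 = 528 asks against 66 × 4 = 264, a ratio of 2:1.

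**2. Effect on reports if each ask covers a fixed window**

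Assumed, not in the article: the same chance p of a report at each ask in both arms, independent between asks. The share with at least one report after k asks is 1 − (1 − p)^k.

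| p per ask (assumed) | TTM, k = 8 | Control, k = 4 | Ratio |
|---|---|---|---|
| 1% | 1 − 0.99^8 = 7.7% | 1 − 0.99^4 = 3.9% | 1.96 |
| 2% | 1 − 0.98^8 = 14.9% | 1 − 0.98^4 = 7.8% | 1.92 |
| 5% | 1 − 0.95^8 = 33.7% | 1 − 0.95^4 = 18.5% | 1.81 |

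In persons at p = 5%, that is 66 × 0.3366 = 22.2 against 66 × 0.1855 = 12.2, with no difference in risk. Equal but incomplete attendance does not remove the gap. With 75% attendance in both arms (assumed), the ratio is 1.97 at p = 1% and 1.86 at p = 5%.

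**3. Effect if each ask covers all time since the last session**

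Eight one-week periods and four two-week periods both cover about 8 weeks. The model in step 2 then does not apply. What remains is better recall over one week than over two, and more frequent prompting. The article gives nothing from which to put a number on that. It would be smaller than the table suggests.

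**4. People who stop attending**

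The sample size is 114 before dropout and 132 after, so the plan allows for the loss of 66 − 114/2 = 66 − 57 = 9 participants per arm. That covers the whole study, so not all 9 need be lost in the 8 weeks. Whoever is lost in that time has fewer asks than the schedule gives, and no replacement enquiry is stated.

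**5. What zero events would show**

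If all 66 in an arm are asked and none reports an event, the exact two-sided 95% upper limit is 1 − 0.025^(1/66) = 5.4%. This limit does not depend on how often people are asked. It does show that observing none is not evidence of none.

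**The case against.** The strongest reply is that the plan makes no between-arm comparison of adverse events. They are neither a primary nor a secondary outcome, Statistical Analysis contains no test of them, and the feasibility hypothesis concerns the TTM programme, which is the arm asked weekly. For that arm the schedule is the more searching one and works against the authors' own hypothesis. This stands. The 8 against 4 imbalance does harm only when counts are set side by side by arm, and the point is not that a planned test is biased.

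A reader might infer that the TTM arm will show about twice the reports. The documents do not support that. The doubling needs the fixed-window reading, and no recall period is given. If the question is about discomfort caused by the session itself, 8 sessions are also twice the exposure, and a higher count would be real.

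A reader might also infer that events in non-attenders and in follow-up are missed. That goes too far. The article condenses a fuller protocol that is not shown. Its withdrawal provision and Table 1 presuppose that some events become known. Retention Strategies describes repeated contact attempts and a secondary contact person, and someone who misses a session can report at the next. What can be said is that no routine enquiry is stated for these people; the contact attempts are described as a means of completing the intervention, without mention of adverse effects. Events between T1 and T2 also lie outside the hypothesis, which is limited to the intervention period.

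Nor does the point undermine feasibility as a whole, since refusal and attendance are measured separately.

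The objection that an article leaves details to the full protocol does not reach the main point. The two schedules and the attachment of the question to sessions are stated outright.

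**Conclusion.** The point holds in a limited form. Followed as written, adverse effects are sought 8 times in the TTM arm and 4 times in the control arm, and less often in anyone who stops attending, with no common enquiry stated at T1. Crude counts should not be compared between arms, and a statement that no adverse events occurred during the intervention would apply to attenders rather than to all randomised.

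The 2:1 ratio of asks follows directly from the article. The excess of roughly 1.8 to 2.0 times in participants with a report rests on three assumptions: a fixed window per ask, equal and independent chances of a report, and a chance of 1% to 5% per ask. Under a since-last-session question the excess is smaller and cannot be quantified from the article.

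The primary and secondary efficacy outcomes are unaffected. This is an inexpensive improvement to an item that the protocol itself places within a primary question.

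**What to change.** 1. At the existing T1 assessment, add one standard adverse-event question covering the 8-week intervention period. The blinded data collectors put it to every randomised participant, and those who stopped attending or were withdrawn are called. Asking it after the outcome scales keeps an answer that reveals the arm from influencing the ratings. It may be repeated at T2 if follow-up events are of interest.
2. Base any between-arm statement on adverse events on this common time point.
3. Keep the session question, state its recall period, and report its results by arm together with the number of asks made.
4. Report the proportion with an event and its exact 95% interval, with the number asked as denominator, instead of a bare statement that none occurred.
5. Add the item to Table 2.

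**Cost.** A few minutes at a visit that already takes place, and some telephone calls; no new visits or staff. Recall over 8 weeks is imperfect in people enrolled for memory impairment, so the T1 question may lose minor events that weekly asking would catch. That is why the session reports should be kept and reported alongside it, not replaced by it.

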**Figure 2 F2:**
[figure not shown]
A flow chart of conducting the TTM-based health education program.

### Outcomes and Measuring Instruments

#### Socio-Demographic Profile

A self-designed sheet will be used to collect the demographic data, including age, gender, education, job, financial status, marital status, living condition, family history of dementia, amount of smoking, amount of alcohol consumption, eating habits, physical activities, cognitive activities, physical health status, and clinical subtype of MCI [tested by the Auditory Verbal Learning Test (Chinese Version) (29) according to the Winblad criteria (30)].

### Primary Outcomes

#### Level of Compliance of Participation in Cognitive Dysfunction Management

The compliance of participation in cognitive dysfunction management will be determined using the Cognitive Dysfunction Management Compliance Scale (31). This scale was developed by our research team. It is composed of six dimensions: (1) perceived susceptibility (seven items); (2) perceived seriousness (four items); (3) perceived benefits (three items); (4) perceived barriers (seven items); (5) cues to action (three items); and (6) self-efficacy (eight items). Each item is scored based on a five-point Likert scale (1=not at all agree; 2=disagree; 3=not concerned; 4=agree; 5=very agree), (–) for reverse counting. A higher score means more adherence to cognitive management. The Cronbach's α coefficient of the overall questionnaire was 0.904, and content validity I-CVI was 0.92.

#### Level of Knowledge of MCl

The scores of MCI knowledge will be determined using the MCI Knowledge Questionnaire. The questionnaire, designed by HY, Pan of Fudan University (32), has three domains: (1) basic knowledge of MCI (four items); (2) risk factors of MCI (eight items); and (3) prevention, treatment, and cognition of MCI (eight items). The answer for each item is true (1) or false (0). Total scores on the questionnaire range from 0 to 20, with higher scores indicating more knowledge. The Cronbach's α coefficient of the overall questionnaire was 0.85, the content validity I-CVI was 0.93 (32).

### Secondary Outcomes

#### General Cognitive Function

The cognitive function will be assessed using the Chinese version of the Montreal Cognitive Assessment Basic (MoCA-B). It was developed as a collaborative project between Canada and Thailand to differentiate between older adults with and without MCI regardless of level of literacy. MoCA-B includes nine domains: executive functioning, memory, language, orientation, counting, abstract, visual perception, naming, and attention (33). According to the Chinese cultural background, the optimal cutoff scores for MCI screening were 19 for individuals with no more than 6 years of education, 22 for individuals with 7 to 12 years' education, and 24 for individuals with more than 12 years of education. The Cronbach's α was reported at 0.807, and the criterion-related validity was 0.787 (25).

#### Theory of Mind

Affective and cognitive Theory of mind (ToM) will be assessed using the “Yoni task” (Chinese version) (34). A total of 103 pictures can be subdivided into three types that correspond to affective ToM, cognitive ToM, and control conditions. A face named “Yoni” is shown in the middle with all pictures. The participant will be asked to complete special tasks depending on Yoni's gaze direction, facial expression and the information contained in the sentence. Correct answers received one point and incorrect answers received zero points (35).

#### Depression Symptoms

Depressive symptoms will be assessed using the Chinese version of the 15—item Geriatric Depression Scale (GDS). The total score ranges between 0 and 15, using seven as the cutoff point, with higher scores indicating severe depression. It has been validated in Chinese populations with reliability (Cronbach's α was 0.89) and validity was 0.96 (36).

#### Apathy Symptoms

Apathy symptoms will be assessed using the 18-item Apathy Evaluation Scale (AES), which involves cognitive, behavioral, emotional, and “other.” Scores range from 18 to 72 with higher scores corresponding to more severe apathy (37). It has been validated in the Chinese older adult population with Cronbach's α 0.89, test retest reliability 0.88, and inter-tater reliability 0.86 (38).

#### Sleep Quality

The Pittsburgh Sleep Quality Index (PSQI) has been widely used to measure subjective sleep quality in older adults with MCI (39, 40). It involves seven components: sleep quality, sleep latency, sleep duration, habitual sleep efficiency, sleep disturbances, use of sleep medication and daytime dysfunction (41). Each component is reflected by a score ranging from 0 to 3, total scores range from 0 to 21. Higher scores indicate worse subjective sleep quality. It has been validated in a Chinese population with Cronbach's α 0.82−0.83, and the test-retest 0.85 (42).

#### Data Collection

Before randomized allocation, the baseline data (T0) will be collected at a community health care center by the staff blinded to group allocation, including socio-demographic profile, primary outcomes and secondary outcomes; primary outcomes, and secondary outcomes will be measured again at the end of the intervention (T1) and 3 months after intervention (T2). Table 2 shows the assessment and timeline of the study.

**Table 2 T2:** Summary of study assessments and time-lines.

	**Questionnaire items**	**Time point**				
		**Baseline**	**Randomized allocation**	**Intervention**	**Post intervention**	**Follow-up 3 months**
		**T0**			**T1**	**T2**
Enrollment						
Eligibility screening						
Informed consent						
Screening	**General information**					
	Demographic information	✓				
	**Daily functions**					
	Activities of Daily Living (ADL)					
	**Neuro psychological examination**					
	Mini-Mental State Examination (MMSE)					
	Montreal Cognitive Assessment Basic (MoCA-B)					
	Auditory Verbal Learning Test (AVLT)					
Measurements						
Primary outcomes	**Compliance of cognitive dysfunction management**					
	Cognitive Dysfunction Management Compliance Scale	✓			✓	✓
	**Level of knowledge of MCl**					
	MCI Knowledge Questionnaire	✓			✓	✓
Secondary outcomes	**General cognitive function**					
	Montreal Cognitive Assessment-Basic (MoCA-B)	✓			✓	✓
	Theory of Mind (ToM)	✓			✓	✓
	**Neuropsychiatric symptoms**					
	Depression Scale Short-form (GDS-15)	✓			✓	✓
	Apathy Evaluation Scale (AES)	✓			✓	✓
	**Sleep quality**					
	The Pittsburgh Sleep Quality Index (PSQI)	✓			✓	✓

#### Retention Strategies

Several safeguards will be put in place to decrease the dropout rate. (1) collecting multiple contact information, including contact information of a secondary contact person; (2) distributing a gift for time spent at baseline and follow up interviews; (3) enrolling in WeChat Group (WeChat, a mobile application, which is an instant messaging application) and receiving reminder messages of upcoming intervention; (4) making multiple contact attempts to complete each intervention; and (5) providing a quiet and comfortable environment for intervention.

### Statistical Analysis

Data collection will be conducted in a single room and kept in a password protected computer folder. Collected data will be encoded in Excel and double-checked. Data processing and statistical analysis will be conducted using SPSS 22.0. Descriptive statistics will summarize demographic data and observable variables using frequencies and percentages for categorical variables, means ± standard deviations for continuous variables. We will employ exploratory analysis (normality testing and distribution curves) to examine the distribution of data. The proportionality of baseline data for both groups will be compared using the non-parametric Wilcoxon test, the Chi–square test, and the *T*-test. A 2 (group) × 3 (time) ANOVA will be used to determine the effect of the group factors, the intervention group and control group differences within-group over time, and interaction effects. Simple effect analysis will be added when there is an interaction between group factors and time factors. The intention-to-treat principle will follow data analysis. A two-tail *P*-value of < 0.05 will be considered statistically significant.

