Health education can improve individual's level of disease knowledge, and it is an essential component of chronic disease management strategies. Health education helps individuals to understand the essence of disease management and encourages individuals to participate in their own disease management (10, 11). Nevertheless, previous studies have shown that older adults in the community still lack knowledge about the cause, diagnosis, and treatment of cognitive impairment. A total of 55.5% of community-dwelling older adults did not perceive themselves as very knowledgeable about dementia; more than 65% thought dementia was caused by healthy aging (12, 13). Meanwhile, older adults with MCI had lower scores with knowledge of dementia than those with normal cognition, and the scores would decrease as cognitive impairment worsened gradually (14). In addition, some limitations also occurred in health education activities aimed at the population with cognitive dysfunction, educators placing more emphasis on patients with dementia and their caregiver rather than those with MCI; the lack of health education programs for older adults with MCI in the community setting (15); and the failure to assess the extent of behavioral change caused by a health education (16). Anghel et al. found that better compliance behaviors were related to increased knowledge of the disease (17). Nevertheless, whether health education can improve the compliance of participation in cognitive dysfunction management for older adults with MCI is not clear.

The trans-theoretical model (TTM) is an integrative model of behavior change that has been applied successfully to improve compliance, self-management, and health behavior in older adults and patients with chronic diseases (18–20). The effectiveness of behavioral changes may increase, framing them with the TTM (18). TTM emphasizes behavior change as a process rather than a single event, which posits that individuals move through five stages of adoption health-promoting behaviors (i.e., pre-contemplation, contemplation, preparation, action, and maintenance) (21). Nevertheless, no education program based on TTM has been proven to promote behavior change and other cognition-related health outcomes on older adults with MCI.

To address this gap, we developed a TTM-based health education program, which was targeted to improve the disease knowledge and the compliance of participation in cognitive dysfunction management for older adults with MCI.

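### Baseline balance is judged by about 22 significance tests and the stated 2 × 3 ANOVA has no covariate, leaving avoidable education variance in the group main effect and any between-group simple effects, chiefly for MoCA-B

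*Protocol article*

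**What the plan says.** All references are to the protocol article.

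- **Baseline comparison.** Statistical Analysis: "The proportionality of baseline data for both groups will be compared using the non-parametric Wilcoxon test", together with the chi-square test and the t-test. The general rule in that section is that a two-tailed p-"value of < 0.05 will be considered statistically significant". It does not say what follows from a significant or non-significant baseline test.
- **What is measured at baseline.** Socio-Demographic Profile: "A self-designed sheet will be used to collect the demographic data, including age, gender, education, job, financial status, marital status, living condition", and further items, 15 in all. Data Collection sets the baseline (T0) data as "including socio-demographic profile, primary outcomes and secondary outcomes", which adds seven outcome scales.
- **Outcome model.** Statistical Analysis names a 2 (group) × 3 (time) ANOVA for the group effect, the change over time and the interaction. It adds: "Simple effect analysis will be added when there is an interaction between group factors and time factors". No covariate is named, and the section does not say in which direction the simple effects run.
- **Education and MoCA-B.** General Cognitive Function: "the optimal cutoff scores for MCI screening were 19 for individuals with no more than 6 years of education", then 22 for 7 to 12 years and 24 above 12 years. The entry criteria in Table 1 use 18, 21 and 23 for three education levels.
- **Allocation.** The randomisation section describes a 1:1 computer-generated list and states no stratification.

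**The concern.** There are two linked problems with the method as stated.

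First, allocation is random, so any baseline difference between the arms is a chance difference. A significance test can then only ask whether chance operated. It raises false alarms at a known rate and passes imbalances that could matter for a prognostic variable. Readers would be told that the arms are or are not comparable on evidence that cannot show it.

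Second, the variables tested for balance are then left out of the outcome model. The protocol's own cut-offs point to education as related to MoCA-B, and education-specific entry thresholds carry that spread into the sample. The Background adds, of dementia knowledge in relation to cognitive status, that "the scores would decrease as cognitive impairment worsened gradually". That makes baseline cognition a plausible, though unquantified, predictor of the knowledge score. What is at stake is precision: between-arm comparisons that use the level of MoCA-B carry variance that a variable already collected could remove.

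**Working it through.** **1. The plan's own figure.** Sample Size gives 114 participants for an independent t-test with d = 0.684, α = 0.05 and power 0.95 (written there as β). A two-sided t-test calculation gives 56.5, so 57 per arm and 114 in total. The figure reproduces and does not depend on this point.

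**2. Number of baseline tests.** The sheet has 15 items: age, gender, education, job, financial status, marital status, living condition, family history of dementia, smoking, alcohol, eating habits, physical activities, cognitive activities, physical health status and MCI subtype. The outcomes at T0 number seven: compliance, knowledge, MoCA-B, Theory of Mind, GDS-15, AES and PSQI. 15 + 7 = 22 (23 if affective and cognitive Theory of Mind are scored separately).

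**3. False alarms under correct randomisation, if the tests were independent.**
- Expected number: 22 × 0.05 = 1.1.
- P(at least one) = 1 − 0.95^22 = 0.676.
- P(at least two) = 0.302.

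The items are likely to be correlated, so these are approximate.

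**4. An imbalance that passes.** Take an education level held by 38 of 66 in one arm and 28 of 66 in the other, a difference of 10/66 = 15 percentage points. The chi-square without continuity correction is 3.03, p = 0.08. If the two levels differed by 3 to 5 points in mean MoCA-B (assumed), the arms would differ by 0.152 × 3 = 0.45 to 0.152 × 5 = 0.76 points. The upper figure needs the whole imbalance to lie between the lowest and highest bands. This is an uncommon draw, given for illustration.

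**5. Which ANOVA terms are affected.** Give each person a constant education offset e.
- **Group × time, with time within-person:** e is the same at all three visits and drops out of every within-person difference. In a simulation (66 per arm, 4,000 runs, person SD 2, residual SD 1.5, effect 0.7, offsets 0/3/5 in equal thirds, all assumed) the interaction F was unchanged to rounding (largest difference 6 × 10⁻¹⁴). Power was 47.9% with and without the offset.
- **Group main effect:** e stays in the person mean. The variance of the offset is 4.22, so the SD of the estimate is √[(2/66)(4 + 2.25/3)] = 0.38 without it and √[(2/66)(4 + 2.25/3 + 4.22)] = 0.52 with it. The simulation gave the same values, and power fell from 24.0% to 14.4%.
- **Between-group simple effects after the intervention (T1) and at three months (T2):** each compares the arms at one visit, so e stays in full. The 95% range of the chance shift is ±1.96 × SD(e) × √(2/66). That is ±0.70 points for equal thirds (SD 2.05), ±0.61 for a 60/30/10 mix (SD 1.80) and ±0.50 for 80/15/5 (SD 1.45).

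**6. Share of variance that education could remove from a T1 MoCA-B contrast.** Share = V / (V + 2.2² + noise²), where V is the variance of the band means, 2.2 the assumed within-band true SD and noise the assumed visit SD.
- **Low end:** mix 50/35/15, a 3-point span with steps in the same proportion as the cut-offs (0/1.8/3), noise 2.5. V = 1.32, and 1.32 / (1.32 + 4.84 + 6.25) = 0.11.
- **High end:** mix 34/33/33, steps 0/3/5, noise 1.5. V = 4.25, and 4.25 / (4.25 + 4.84 + 2.25) = 0.37.

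**7. If T0 MoCA-B were already a covariate.** In a simulation on these ranges (n = 132, 3,000 runs) the variance with T0 and education was 0.92 to 0.99 of that with T0 alone, a further gain of 1–8%.

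**The case against.** The case on the other side is substantial, and much of it stands.

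- **The interaction is unaffected.** A reader might infer that education remains as noise in every result. On the ordinary reading of a 2 × 3 design, with time within-person, that is untrue of the interaction, which also decides whether simple effects are run. Simple effects of time within a group would be unaffected too. The article does not use the term repeated measures, but nothing in it requires the less favourable reading.
- **Five points is a difference in cut-offs.** A reader might take 24 − 19 = 5 as the effect of education. It is a difference between screening thresholds for a secondary outcome, and every participant must also score at least 24 on the MMSE, which could narrow the spread. The documents give no education effect on compliance or knowledge, and the Background remark concerns cognitive status.
- **No bias.** A reader might infer confounding. Under randomisation the unadjusted contrast is unbiased, and its standard error already allows for chance imbalance.
- **The baseline tests have no stated consequence.** The plan does not use them to choose covariates or to judge efficacy, so the 68% does not pass into any trial conclusion. The section also already plans descriptive summaries.
- **A missing covariate list is not a fault in a condensed article.** That is right, and the point does not rest on it. It rests on two methods that the article does state: baseline testing, and an ANOVA on group and time alone.

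What the objection leaves untouched is that the baseline tests are uninformative, and that the group main effect and any between-group simple effects are less precise than they need be.

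**Conclusion.** The point holds in a limited form. The baseline tests cannot establish comparability, with about a two-in-three chance of at least one p < 0.05 under correct randomisation if they were independent. The stated ANOVA leaves avoidable variance in the group main effect and in any between-group simple effects at T1 and T2, chiefly for MoCA-B.

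The size rests on assumed within-band SD, visit noise, education mix and a 3–5 point education gap. On those assumptions it is about 11–37% of the residual variance of an unadjusted T1 MoCA-B contrast, and about 1–8% if T0 MoCA-B is already in the model. The stated ANOVA uses T0 as a level of time, not as a covariate. For compliance and knowledge the size is unknown.

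The documents do not support a claim of bias, of damage to a within-person interaction test, or of a demonstrated loss on the primary outcomes. This is a worthwhile improvement to the model, not a threat to the trial's validity.

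**What to change.** 1. State in the analysis section that between-group comparisons include education band (the three bands already used for MoCA-B) and age as fixed covariates, whatever imbalance is observed. Fix this before allocation is unblinded.
2. Report the unadjusted result as a sensitivity analysis.
3. Adding T0 MoCA-B to the knowledge model is optional, because the documents give no correlation on which to judge the gain.
4. Present baseline data by arm descriptively. Do not use baseline p-values to judge balance or to choose covariates.

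**Cost.** One or two sentences, no new data, and three or four degrees of freedom out of more than 110. For outcomes unrelated to education or age there may be no gain.
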